## Abstract

**Background:**

Vitamin D deficiency is associated with cardiovascular (CV) risk in multiple populations, including those with chronic kidney disease (CKD). The active form of the hormone (1,25 OH_2_D_3)_ binds to receptors in multiple organs. CKD patients are deficient in both 25 Vitamin D and 1,25 OH_2_D_3_. Clinical trial data demonstrating the benefits of vitamin D formulations are limited, and fail to show significant benefits on CV outcomes, and have compared different compounds, in various populations, and focused on a variety of outcomes. A understanding of the mechanism by which different vitamin D compounds confer CV protection in CKD is important for the design of future studies.

**Methods/Design:**

This 3 arm randomized prospective double-blinded placebo-controlled study examining the impact of calcitriol (1,25 OH_2_D_3_) and 25-hydroxyvitamin D3 supplementation compared to placebo on vascular stiffness, as measured by pulse wave velocity (PWV). Patients are enrolled from 2 tertiary care institutions if they meet inclusion criteria (stable estimated glomerular filtration rate (eGFR) between 15-45ml/min, <±5ml/min change in previous 6 months), on stable doses of renin-angiotensin aldosterone system blockade. For those already receiving vitamin D therapies, a 3 month washout period before randomization is mandatory. Treatment duration is 6 months; medications are given thrice weekly in fixed doses. The primary outcome measure is Vascular stiffness, measured non-invasively by pulse wave velocity (PWV). Other measurements include BP, kidney function and serial blood levels of biomarkers. The primary analysis will compare any vitamin D therapy versus placebo for the primary outcome defined as the change of PWV from baseline to 6 months. Analysis of covariance will be used to detect differences between vitamin D preparations in the magnitude of reduction in PWV.

**Discussion:**

This study is novel in that we are using a robust study design in CKD patients (not on dialysis) comparing placebo to different forms of vitamin D supplementation in fixed doses, irrespective of baseline values. We hope to demonstrate the biological mechanistic effect of vitamin D supplementation on vascular function in order for this information to be used in designing larger randomized controlled trials.

**Trial registration:**

Current Controlled Trials NCT01247311. Date of Registration: November 12, 2010.

**Electronic supplementary material:**

The online version of this article (doi:10.1186/1471-2261-14-156) contains supplementary material, which is available to authorized users.

## Background

Cardiovascular (CV) disease in chronic kidney disease (CKD) is highly prevalent and is associated with a significant increase in morbidity and mortality [1]. Vascular dysfunction and CV disease are caused by a combination of atherosclerotic processes (mediated by dyslipidemia and smoking) and arteriosclerotic processes such as aging, diabetes, vitamin D deficiencies, hyperphosphatemia and hyperparathyroidism (HPTH). The latter is associated with vascular stiffness, loss of collagen and elastin fibers [2]. CKD patients have both ‘conventional’ and non-conventional risk factors for CV disease; and high prevalence of left ventricular hypertrophy (LVH) has been noted. To date, conventional CV disease risk reduction agents and strategies (renal angiotensin aldosterone system (RAAS) antagonists, anti-platelet agents, lipid lowering agents) have either not been systematically evaluated in all CKD populations, or do not appear to mitigate CV disease risk to the extent that they are effective in non-CKD populations. Furthermore, strategies to address non-conventional risk factors (anemia, hyperphosphatemia) on outcomes have either shown no impact, harm, conflicting results, or have not been evaluated in a rigorous randomized control trial with clinically meaningful endpoints [3].

Vitamin D deficiency, (25 OHD_3_) is common in both CKD and general populations. It has been associated in animal and human studies with hypertension (HTN), diabetes, obesity and inflammation, and proteinuria. It is these associations that has led some to regard it as an important CV disease risk factor [4–6]. CKD patients have low levels of 25-hydroxyvitamin D (25 vitamin D), but also lack the physiological capacity to hydroxylate 25 vitamin D into its active form 1,25-dihydroxyvitamin D (1,25 vitamin D), which binds to the vitamin D receptors (VDR) found in blood vessels, the heart, muscles and kidneys. Animal studies describe the impact of VDR activators on inflammation in both kidneys and hearts. In addition, LVH has been noted, and reversed with supplementation [7]. [ Human studies have demonstrated reduction in proteinuria [8, 9] and some impact on changes in eGFR. These are small studies of limited duration. Thadhani et al. have found that treatment with paricalcitol (a VDR activator) in CKD patients reduces parathyroid hormone (PTH) levels within 4 weeks of commencing treatment versus a placebo [10], however, did not impact the primary outcome ( LV mass), but did reduce the number of CV disease-related hospitalizations over the trial period. Large cohort studies have also demonstrated reductions in 1,25 vitamin D and 25 vitamin D in CKD populations in association with rises in serum PTH values [11], at eGFR levels commencing around 50mL/min/1.73m^2^. While CKD patients may be able to hydroxylate 25 vitamin D outside the kidney, the relative effectiveness of these mechanisms have not been studied [2]. The prevailing theory is that the combined 25 OHD_3_ and 1,25 OH_2_D_3_ deficiencies seen in CKD do impact outcomes.

The association between 25 vitamin D deficiency and CV disease has been demonstrated in numerous populations [5, 12]. The active hormone modulates a variety of processes directly associated with arteriosclerotic changes via its interactions with specific biomarkers and inflammatory processes [13–17]. As a recent Cochrane review asserts, no prospective randomized controlled study to date have demonstrated the effect of vitamin D supplementation to reduce CV disease events [18]. Given the multiple reported effects of vitamin D on PTH, phosphate (PO_4_), blood pressure (BP), inflammation, insulin sensitivity and other factors, it is imperative to demonstrate a biological impact of vitamin D on vascular function, which could be directly in the causal pathway for CV disease [11, 15, 19, 20].

There are non invasive methods of studying vascular stiffness, the most used of which is Pulse wave velocity (PWV) using standardized validated equipment ( aSphygmoCor). This technique utilizes applanation tonometry to measure the velocity of the pulse wave between two points on the arterial tree [21]. Increased vascular stiffness ( higher PWV values) is associated with LVH, poor CV disease outcomes, and death in dialysis populations [22, 23]. The reproducibility and validity of this measurement has been demonstrated both in the general population and in those with kidney failure [22, 24, 25]. Utilizing PWV measurements, we will attempt to demonstrate changes in vascular stiffness with various forms of vitamin D supplementation in a non dialysis CKD population.

## Methods/Design

### Overarching objectives

The overarching objective of this study is to describe the impact of currently used formulations of vitamin D (25 vitamin D3 and calcitriol) on vascular stiffness in patients with CKD, eGFR levels between 15 and 45 mL/min/1.73m^2^. We hypothesize that supplementation with vitamin D analogues will result in greater reductions in PWV measurements than placebo when compared to baseline measurements.

### Study cohort

Subjects will be drawn from a cohort of CKD patients treated according to best practices at university based tertiary care centers in Vancouver. Following written informed consent, subjects who fulfill eligibility criteria at screening (Table 1) will be randomized (1:1:1) to receive treatment of 25 vitamin D3 at 5000IU three times a week, 1,25 vitamin D (calcitriol) at 0.5ug three times a week, or placebo.

**Table 1 Tab1:** **Inclusion/exclusion criteria**

Inclusion criteria	Exclusion criteria
- Signed informed consent	- Refused informed consent
- eGFR between 15-45 ml/min	- Change of >5ml/min eGFR over the past 6 months
- Change of <5ml/min in eGFR over the past 6 months	- Planned transplant within 6 months
- Treated with maximal conventional CV disease risk reduction protocolized medications (ACEi or ARB)	- Likely to commence renal replacement therapy within 6 months after enrolment
- Currently receiving vitamin D therapies, but agreeing to a washout period of 3 months	- Terminal malignancies
	- Active infections
	- Active inflammatory diseases (SLE, vasculitis)

### Statement of purpose

This physiological study will describe the impact of vitamin D therapies on a physiological measure related to CVD in CKD: vascular stiffness. Describing this mechanism would enhance the viability of testing longer term outcomes using these interventions.

*Primary questions:*Does treatment with vitamin D analogues for a period of 6 months reduce PWV in CKD patients as compared to placebo?

*Secondary questions:*Is there a difference between 1,25 vitamin D and 25 vitamin D formulations in the magnitude of reduction in PWV?Does 6 month provision of 1,25 or 25 vitamin D lead to demonstrable reductions in BP (without changes in antihypertensive medication), or proteinuria (without change in ACEi/ARB therapy) relative to placebo?What is the impact of 1,25 vitamin D and 25 vitamin D on blood levels of FGF-23, serum PTH, PO_4_ Ca, and CRP in this population? Is there a relationship between changes in vascular stiffness and changes in these biochemical/hormonal parameters?

### Rationale for the study

There is increasing evidence that vitamin D acting on multiple aspects of the physiological processes involved in the pathogenesis of CVD may be an important therapeutic strategy in CKD. The intellectual appeal of studying vitamin D supplementation in CKD has led to a number of proposals for studies of CV outcome in CKD, and some randomized control trials [3, 10, 26, 27]. While these studies have shown promising signals (reduction in proteinuria and reduction in CV hospitalization and events), no studies have addressed the mechanism of how vitamin D supplementation might impact these outcomes in humans, other than via reduction in LV mass (which was not shown). While both 1,25 vitamin D and 25 vitamin D formulations have been used in clinical studies to date, controversy continues as to the form of vitamin D best used in clinical practice to supplement deficiencies [16, 28, 29].

Recent meta-analyses and systematic reviews [15, 17, 26, 30–32] have described epidemiological associations with 25 vitamin D deficiencies and outcomes, and supplementation as impacting intermediate outcomes (proteinuria), but not mortality or time to end stage kidney failure. Quantification of the impact of vitamin D on vascular stiffness will permit estimates of effect size and stimulate further research into combining medication strategies.

### Interventions

We will prescribe fixed does of 5000IU 25 vitamin D and 0.5μg of 1,25 vitamin D, three times a week, (compatible with doses given in other studies, and at intervals used in many clinical practices) in order to maximally stimulate the circadian impact of the vitamin D therapy. A 6 month treatment period is chosen to ensure “biologically meaningful exposure” which should permit measurable changes in blood levels and vascular compliance, as well as mitigate the effects of sun exposure. Medications are supplied in oral suspension with identical look and taste (in almond oil), so that patients and providers are blinded.

### Duration of the study

Each patient will be followed for a period of 6 months post-randomization. Patients on existing vitamin D supplementation will have been followed for 9 months due to the additional 3 months of washout prior to randomization.

### Study design

This will be a 3 arm prospective randomized double blind placebo controlled study of 128 stable CKD subjects examining the impact of vitamin D supplementation (1,25 vitamin D or 25 vitamin D formulations) compared to placebo on arterial stiffness and other parameters of vascular health. The study plan shown in Figure 1 will combine physiological experiments in a well characterized cohort of patients with CKD, and utilize observational study methods to test and explore additional related hypotheses.

**Figure 1 Fig1:**
[figure not shown]
**The study plan depicts the timeline for the completion of the study.** Screening/recruitment includes the 3 month washout period. Vitamin D doses will be administered for 6 months allowing for the inclusion criteria. PWV will be measured at baseline (-3 months), post washout period (0 months) and post treatment (6 months) for both treatment arms and their respective placebos.

### Sample size considerations

The study is powered to demonstrate differences in primary outcome between individual study subjects; the calculated sample size will be adequate to detect a clinically important effect of vitamin D on PWV (reduction of 1m/sec). The mean difference of 1m/s is clinically meaningful in that it has been demonstrated to confer a 34% increased risk of CV mortality in a cohort of CKD stage 5 patients on dialysis [33, 34]. A sample size of 105 (35 placebo arm and 70 treatment arm) without attrition will provide 85% power to demonstrate the mean PWV difference of 1m/s between arms, with 0.05 target alpha for a two sided test. Thus, recruitment and enrolment of 128 subjects will allow for ~15% attrition.

### Trial management

To ensure safety and data integrity, the single research office centrally located is responsible for the conduct at two sites within the city, both University teaching hospitals. The study will be overseen by independent Data Safety and Monitoring Board (DSMB) and also will review subject lab results and concomitant medications on a monthly basis. The DSMB will screen for the adverse events, including the possibility of hypervitaminosis, hypercalcaemia and hyperphosphatemia. In addition, random audits will be performed to assess data quality.

### Variables measured

PWV measurements, clinical and biological samples will be obtained at pre-washout, baseline, and post treatment (3 time points). Blood and urine samples will be obtained at each of the 3 time points to test for serum PTH, 1,25 vitamin D, 25 vitamin D, fibroblast growth factor-23 (FGF-23), PO_4_, calcium (Ca), C-reactive protein (CRP), urinalysis and random urine albumin-to-creatinine ratio (UACR). All samples will be run in an accredited laboratory using validated assays. BP will be done in duplicate and PWV will be done in triplicate at each visit using standardized BP cuffs and SphygmoCor, respectively [35]. Clinical and medication histories as well as rationale for specific biomarkers are listed in Additional file 1.

### Statistical analysis

The primary analysis will compare vitamin D (25 vitamin and 1,25 vitamin D) therapies versus placebo for the primary outcome defined as the change of PWV from baseline to 6 months by covariance analysis (ANCOVA); where the 6 month measurement of PWV will be the dependent variable, allocated treatment the independent variable, and baseline PWV the baseline covariate [29, 36, 37]. Analyses will be considered statistically significant if the p-value is <0.05 for allocated treatment. In case of violation of ANCOVA assumptions we will use a mixed model approach.

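### For patients measured at month -3, the primary ANCOVA uses one of two pre-randomisation PWV values and no use is stated for the other: a minor, near-free gain in precision is missed

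*Protocol article*

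**What the plan says.** - **Schedule.** The Figure 1 legend states: "PWV will be measured at baseline (-3 months), post washout period (0 months) and post treatment (6 months". Variables measured lists the same three occasions: "PWV measurements, clinical and biological samples will be obtained at pre-washout, baseline, and post treatment (3 time points". It adds that "PWV will be done in triplicate at each visit".
- **Who has the early visit.** The abstract (Methods/Design) ties the washout to prior users: "For those already receiving vitamin D therapies, a 3 month washout period before randomization is mandatory". Duration of the study agrees: "Patients on existing vitamin D supplementation will have been followed for 9 months due to the additional 3 months of washout prior to randomization". Table 1, however, has this among the inclusion criteria: "Currently receiving vitamin D therapies, but agreeing to a washout period of 3 months".
- **Primary model.** Under Statistical analysis, month 6 PWV is the dependent variable, with "allocated treatment the independent variable, and baseline PWV the baseline covariate". The fallback is: "In case of violation of ANCOVA assumptions we will use a mixed model approach". The visits that would enter the mixed model are not named.
- **Label.** The Figure 1 legend attaches the word baseline to month -3. Variables measured separates pre-washout from baseline, so there baseline is the post-washout visit.

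**The concern.** A patient with a month -3 visit contributes two PWV visits before allocation, each in triplicate. The model adjusts for one of them. PWV at a single visit is an imperfect measure of a patient's underlying stiffness, so a second pre-randomisation value may explain some of the variation in month 6 PWV that the first leaves over. Allocation cannot affect it, so adjusting for it introduces no bias and leaves the treatment contrast unchanged.

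What is at stake is precision in the comparison of pooled vitamin D with placebo. Strengths and weaknesses concedes that the study may turn out underpowered, and Sample size considerations gives no standard deviation from which to judge the margin. Gains that need no extra patient or visit therefore deserve a look.

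**Working it through.** **1. The plan's own figure.** Sample size considerations gives 35 placebo and 70 treated patients, a difference of 1 m/s, two-sided alpha 0.05 and 85% power. No SD is given, so the figure can only be solved backwards:

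SD = 1 / [√(1/35 + 1/70) × (1.960 + 1.036)] = 1 / (0.2070 × 2.996) = 1.61 m/s.

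The stated 105 is consistent with an SD of about 1.6 m/s but cannot be confirmed. Below, the 85% is assumed to apply to the ANCOVA with one baseline. If a change multiplies the residual variance by q, then power = Φ(2.996/√q − 1.960).

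**2. Equal correlations, every patient measured twice (assumption).** Let r be the correlation between any two visits. The residual variance, as a share of the total, is 1 − r² with one baseline and 1 − 2r²/(1 + r) with two. The ratio is q = (1 + 2r)/(1 + r)².

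| r | q | Power | Evaluable N for 85% (105q) |
|---|---|---|---|
| 0.3 | 0.947 | 86.9% | 99 |
| 0.5 | 0.889 | 88.8% | 93 |
| 0.7 | 0.830 | 90.8% | 87 |
| 0.8 | 0.802 | 91.7% | 84 |

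**3. Month -3 less informative (assumption).** Month -3 lies nine months before the outcome and before the washout; month 0 lies six months before the outcome and after it. Let a be the correlation of month 0 with month 6, b that of month -3 with month 6, and c that between the two early visits. Then q = 1 − (b − ac)² / [(1 − a²)(1 − c²)].

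- a = 0.7, b = 0.6, c = 0.7: q = 1 − 0.11²/(0.51 × 0.51) = 0.953, power 86.6%.
- a = 0.7, b = 0.49, c = 0.7: b = ac, so q = 1.00 and power stays at 85.0%.

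**4. Only a fraction f has the month -3 visit (assumption, r = 0.7).** A precision-weighted approximation is q = 1/[f/0.830 + (1 − f)].

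- f = 0.50: q = 0.907, power 88.2%.
- f = 0.25: q = 0.951, power 86.7%.

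These are somewhat generous for a plain missing-indicator fit, in which patients with and without the visit share one month 0 slope. There the month -3 slope is k = (r − r²)/(1 − f r²), the month 0 slope is r − f k r, and the residual variance is 1 − r(r − f k r) − f k r.

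- f = 0.50: k = 0.21/0.755 = 0.278, month 0 slope 0.603, residual 0.481, q = 0.481/0.51 = 0.943, power about 87.0%.
- f = 0.25: k = 0.21/0.8775 = 0.239, month 0 slope 0.658, residual 0.497, q = 0.975, power about 85.9%.

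**5. If the 85% was computed without any baseline adjustment.** The one-baseline ANCOVA then already has more power, and the second value adds less: 93.3% to 95.6% at r = 0.5, and 98.7% to 99.6% at r = 0.7.

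**The case against.** The strongest reply is that nothing here is wrong. ANCOVA on one baseline is a standard, unbiased analysis; further covariates are often left to an analysis plan that is not shown; and triplicate readings already reduce within-visit error. All of that stands, and it is why the point is minor. It does not remove the point, because the article itself fixes the covariate and names only one.

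Three stronger readings are tempting, and the documents do not support them.

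- A reader might infer from the Figure 1 legend and Variables measured that every patient is measured twice before randomisation. The abstract and Duration of the study limit the washout to prior vitamin D users. Table 1 can be read either way, so the share is unknown.
- A reader might infer that the extra visit informs no endpoint. The article is only silent. The mixed-model fallback could include it, Study design announces additional exploratory hypotheses, the Discussion plans phenotyping that includes PWV, and the same visit collects biomarkers and brackets the washout.
- A reader might infer that an 11-20% fall in variance is the expected gain. That needs equal correlations over intervals of three, six and nine months, across a change in vitamin D exposure, with full attendance at month -3. Modest decay alone cuts the fall to about 5%, and it can be zero.

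**Conclusion.** The point holds as a minor efficiency matter. Where a month -3 visit exists, two pre-randomisation PWV values are collected, the primary model adjusts for one, and no analysis use is stated for the other. The planned ANCOVA remains valid, and no bias or loss of type I error control is alleged.

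The reduction in residual variance ranges from 0% to about 20%, which takes 85% power to between 85% and about 92%. That range rests on assumed correlations and on applying the 85% to the one-baseline ANCOVA. Its upper part also needs every patient to have the month -3 visit.

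The conflicting use of the word baseline is a related weakness: as written, the one covariate and the start of the change are not uniquely identified. The sections need to be reconciled on that, and on which patients attend at month -3.

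**What to change.** In Statistical analysis, prespecify month 0 (post-washout) PWV as the main baseline covariate in the primary ANCOVA of month 6 PWV, and add month -3 PWV as a second covariate. For patients without a month -3 visit, use a missing indicator with a constant fill-in. This is acceptable because whether the value exists is settled before allocation. Align the baseline label in the Figure 1 legend and Variables measured with this choice, and state which patients have the month -3 measurement.

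The cost is a sentence or two of wording and one or two degrees of freedom out of about 105 evaluable patients. No visit, patient or measurement is added, and the endpoint does not change. The covariates should be fixed before unblinding, since choosing them afterwards would be open to challenge.

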We expect to find vitamin D to have an impact on vascular stiffness and BP irrespective of serum vitamin D levels. The impact will be greatest on those with highest PWV. The data generated herein will permit the development of a set of phenotypes using clinical and biomarker data. Such that characterization of patients according to PWV, BP, FGF-23 and vitamin D levels will be possible, and results of treatment strategies will be examined within the phenotype category. This information will be significant for future enrolment in clinical trials. The biomarker analyses will aid in explaining any dissociation found between BP and vascular stiffness.

Before large randomized trials can be developed, these unanswered questions regarding the mechanism of disease require resolution to ensure pertinent study design. This is an ‘intermediate’ study which fully examines the physiological consequences of different vitamin D therapies in CKD populations. The findings will be used to understand physiological mechanisms, generate further hypotheses for testing, and ultimately contribute to evidence base studies which will inform clinical practice.

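### The primary ANCOVA is valid for the total effect on PWV but cannot separate vessel-wall change from lower blood pressure, and the BP and proteinuria questions carry an undefined condition of no medication change after randomisation

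*Protocol article*

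**What the plan says.** **Primary model.** Under Statistical analysis, the protocol article compares vitamin D (both forms pooled) with placebo by ANCOVA on 6-month PWV, with "allocated treatment the independent variable, and baseline PWV the baseline covariate". No BP term appears in any PWV model described.

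**Purpose.** The Statement of purpose is mechanistic: "This physiological study will describe the impact of vitamin D therapies on a physiological measure related to CVD in CKD: vascular stiffness". The primary question in the same section is narrower: whether six months of treatment lowers PWV relative to placebo.

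**Blood pressure.** Under Variables measured, "BP will be done in duplicate and PWV will be done in triplicate at each visit". The Discussion states: "We expect to find vitamin D to have an impact on vascular stiffness and BP irrespective of serum vitamin D levels". It also foresees that the two may diverge, and refers this to the biomarkers: "The biomarker analyses will aid in explaining any dissociation found between BP and vascular stiffness".

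**Secondary questions.** The Statement of purpose asks whether six months of either form will "lead to demonstrable reductions in BP (without changes in antihypertensive medication), or proteinuria (without change in ACEi/ARB therapy) relative to placebo". The article does not say what happens to patients whose medication does change. Trial management says that the oversight "will review subject lab results and concomitant medications on a monthly basis", so changes should be on record.

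**The concern.** Two separate issues share one source: a variable that treatment may alter after randomisation.

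1. **Attribution of a PWV effect.** PWV depends on the distending pressure when it is measured. This is general physiology; the article does not state it. If vitamin D lowers BP, PWV can fall with no change in the arterial wall. The article offers only biomarker analyses to explain a divergence of BP and stiffness, and these do not take pressure out of PWV. A positive result would support the claim that PWV fell, but not by itself the claim that the vessel became less stiff.

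2. **The medication condition.** Changes in antihypertensives or ACEi/ARB therapy occur after randomisation and plausibly depend on BP or proteinuria, which are the outcomes in question. If the condition is applied by dropping patients with changes, and vitamin D works, more high-BP patients are lost from placebo than from the active arms. The groups then compared are no longer those that randomisation made, and a real effect looks smaller.

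**Working it through.** **Step 1. The plan's own figure.** Sample size considerations gives 35 placebo and 70 treated, a difference of 1 m/s, two-sided alpha 0.05 and 85% power. No SD is stated, so it is solved for:

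SD = 1 / [(1.960 + 1.036) × √(1/35 + 1/70)] = 1 / (2.996 × 0.2070) = 1.61 m/s.

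With SD 1.6 the same formula returns N = 105. The figure is therefore self-consistent but not independently reproducible. It serves below only as the base for the precision gain.

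**Step 2. What leaving out baseline BP costs.** Under randomisation, ANCOVA on baseline PWV is unbiased for the total treatment effect, so omitting baseline BP costs precision only. If baseline mean arterial pressure explains a share R² of the variance left after baseline PWV, the SD becomes 1.61 × √(1 − R²). Assumed R² values:

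| R² | Power at 35 v 70 |
|---|---|
| 0 | 85.0% |
| 0.05 | 86.7% |
| 0.10 | 88.5% |
| 0.20 | 91.8% |

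**Step 3. How much PWV change pressure alone could produce.** The documents give neither a PWV-BP slope nor an expected fall in mmHg; both are assumed.

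PWV change = slope × fall in pressure.

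- 0.03 m/s per mmHg × 3 mmHg = 0.09 m/s
- 0.10 m/s per mmHg × 5 mmHg = 0.50 m/s
- Wider range: 0.03 × 2 = 0.06 m/s, to 0.10 × 8 = 0.80 m/s

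Against the 1 m/s target this is about 10 to 50%, or 6 to 80% over the wider range.

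**Step 4. What restriction to unchanged patients would do to the BP comparison.** All inputs are assumptions. Baseline SBP has mean 135 and SD 15; interim SBP correlates 0.6 with baseline, and final SBP 0.8 with interim. Allocation is 2:1, the true effect is -5 mmHg, and medication changes when interim SBP exceeds a threshold. Estimates are baseline-adjusted. The last column assumes that added drugs lower SBP by 5 to 10 mmHg.

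| Threshold (mmHg) | Medication changed, placebo v active | Unchanged patients only | All randomised, drugs lower SBP by 5 to 10 |
|---|---|---|---|
| 140 | 37 v 25% | -3.46 | -4.44 to -3.85 |
| 145 | 25 v 16% | -3.78 | -4.55 to -4.08 |
| 150 | 16 v 9% | -4.10 | -4.68 to -4.35 |

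Repeat runs moved the restricted estimates by up to about 0.06. The shortfall from restriction is 1 − 3.46/5 = 31% at 140 and 1 − 4.10/5 = 18% at 150. If medication change had no effect on BP, the all-randomised estimate would be -5.0. With a true effect of zero, both analyses gave zero.

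A second model (SD of BP change 12 mmHg, chance of escalation rising smoothly with BP) gave -3.1 to -3.5 under restriction for a true -5, and -1.8 to -2.1 for a true -3. With added drugs lowering BP by 10 mmHg, the all-randomised estimates were -3.7 to -4.0 and -2.2 to -2.4.

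No calculation was made for proteinuria. The same reasoning applies, but its size is unknown.

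**The case against.** **On the primary model.** A reader might infer that the primary analysis is biased or invalid because BP is missing. The article does not support this. Its primary question is whether PWV falls relative to placebo, and the randomised ANCOVA answers exactly that. Nor would baseline mean arterial pressure cure the attribution problem: a value taken before treatment cannot remove a fall that happens afterwards. Six-month pressure could address it, but it is a possible mediator and does not belong in the primary model. The article also collects BP at every PWV visit, asks about BP separately and acknowledges possible divergence, and an analysis plan that is not shown may hold a BP-adjusted analysis. All of this stands. What remains is a limit on the mechanistic conclusion.

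**On the medication condition.** A reader might also infer that patients whose medication changes will be excluded. Nothing in the article says so. The parentheses could equally mean that background therapy is meant to stay stable, or that a BP fall should not be explained by added drugs. The first of these fits the Abstract's requirement of stable renin-angiotensin blockade and Table 1's requirement of maximal ACEi or ARB treatment. So the text supports an undefined condition, not a definite exclusion.

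**On the simulations.** The escalation thresholds are invented. Analysing everyone is not free of dilution either: if added drugs lower BP, that estimate also moves toward zero, and its advantage over restriction narrows to about 0.3 to 1.0 mmHg in the table above. With no true effect, restriction creates none. These points stand too. The case for analysing all randomised patients is that it keeps the randomised comparison, not that it recovers the full -5.

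**Conclusion.** The point holds as a limit on interpretation and an unsettled definition. It is worth correcting but does not threaten the primary test.

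- **PWV.** The primary ANCOVA can show that vitamin D lowers PWV; it cannot show that this reflects the vessel wall. Pressure alone might account for about 0.1 to 0.5 m/s of the 1 m/s target, entirely under assumed slopes and BP falls. If BP does not differ between arms, the ambiguity largely disappears.
- **BP and proteinuria.** If the condition is applied by exclusion, a real BP effect would be understated, by 18 to 31% in the threshold model and by 30 to 38% in the second model for a true -5 mmHg (3.5/5 and 3.1/5). These sizes depend on the assumed escalation pattern. Under a true null there is no bias, so false positives are not at issue.

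Confidence is medium, because the slope is not in the documents and the analysis plan is not shown.

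**What to change.** 1. Keep the primary ANCOVA and add baseline mean arterial pressure as a covariate, with precision as the stated reason.
2. Prespecify one supportive ANCOVA that also includes 6-month mean arterial pressure. Label it explanatory, and say that it conditions on a possible mediator and does not replace the primary analysis.
3. Define the BP and proteinuria comparisons in all randomised patients regardless of medication change. State that this estimates the effect including any such changes and may be diluted by them.
4. Tabulate antihypertensive and ACEi/ARB changes by arm. Keep any restriction to unchanged patients as a sensitivity analysis only.

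The cost is wording and two model terms. BP is already collected at each PWV visit and concomitant medication is already reviewed monthly. Sample size and patient management do not change.
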